### Study variables

#### Primary variable (endpoint)

Difference in rectal preservation rate between CRT–TEM and TEM at 3 years after surgery. The database will be locked after all randomized patients have completed a minimum of 3 years of follow-up for the primary endpoint assessment.

Rectal preservation failure is defined as any completion TME due to protocol discontinuation criteria (e.g., adverse pathology or inadequate response) and/or any salvage TME performed for local recurrence during follow-up.

Local recurrence will be considered a rectal preservation failure irrespective of the subsequent management strategy (including cases treated without TME). Any TME performed for any reason during the 3-year follow-up (including postoperative complications, patient preference, or conversion to abdominal surgery resulting in TME) will be classified as rectal preservation failure. A temporary diverting stoma does not constitute rectal preservation failure; however, a permanent stoma at 3 years (even in the absence of TME) will be classified as rectal preservation failure. Death before 3 years and losses to follow-up will be handled under the ITT framework; in the primary analysis, patients without documented rectal preservation status at 3 years will be conservatively counted as failures, with sensitivity analyses using alternative assumptions. Patients who do not undergo TME for any reason but have persistent/uncontrolled primary disease will be counted as rectal preservation (rectum in situ) but will be recorded as local failure and as non–disease-free (DFS event).

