There are several classifications used to assess submucosal invasion (Haggitt, Kikuchi, Ueno, Kudo, and Kitajima); however, they present limitations and relevant variability that may influence clinical decision-making. Therefore, our group has proposed the Taulí-pT1 classification, which quantifies tumor invasion according to the area of residual healthy submucosa in the specimen, using a uniform methodology based on a percentage derived from a constant reference point [11]. This classification shows excellent correlation with Kitajima’s and very good correlation with Kudo’s system. Its only requirement for applicability is the presence of the muscularis propria in the specimen. Recently, we have published its validation through interobserver concordance analysis [13].

Recent studies with large cohorts and long-term follow-up (although with retrospective designs) have reopened the debate on local surgery for pT1N0M0 rectal cancer. Leijtens et al. [14] reported, in a series of 150 patients with a median follow-up of 58.9 months, a local recurrence (LR) rate of 22.7% and an overall survival (OS) of 82%; even when stratifying tumors without adverse prognostic features, LR rates exceed 20%. Recently, we have published our long-term follow-up cohort, with a median follow-up of 91 months (IQR: 84), 17 patients (16.3%) developed LR and 14 (13.5%) developed distant recurrence. Five-year rectal cancer–specific and overall survival rates were 95% and 74%, respectively. Among the 88 patients without histopathological or surgical high-risk factors, 13 (14.8%) experienced LR and 9 (10.2%) distant recurrence [15].

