## Methods

### Study design

Phase III, multicenter, prospective, controlled, randomized superiority clinical trial evaluating the efficacy and safety of preoperative CRT followed by LE (CRT-TEM group) versus LE alone (TEM group) in clinically staged cT1N0M0 rectal cancer, with rectal preservation as the primary outcome.

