### Sample size

The sample size calculation is based on the primary endpoint, rectal preservation, defined as the absence of the need for completion TME due to discontinuation criteria or local recurrence and rescue to TME. The assumptions are based on data from our group: in T1 tumors, the sm3 rate is 35–40%, with 5–10% of patients presenting adverse pathological factors; in the TAUTEM trial (T2–T3ab), the pCR rate was 44%, therefore a pCR > 55% is expected in T1 cases [22]. Assuming a two-sided test for difference in proportions with α = 0.05 and β = 0.20 (power 80%), 53 patients per group are required to detect as significant a difference between p₁ = 0.60 (TEM) and p₂ = 0.85 (CRT–TEM). Considering a 10% dropout rate, the total sample size will be 106 patients.

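### Counting every undocumented 3-year status as a failure is called conservative, but this is not assured in a superiority test; at the plan's own 10% loss, power falls to about 70%.

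*Protocol article*

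**What the plan says.** Under Primary variable (endpoint), the article opens the rule with "Death before 3 years and losses to follow-up will be handled under the ITT framework" and continues, for the primary analysis, with "patients without documented rectal preservation status at 3 years will be conservatively counted as failures, with sensitivity analyses using alternative assumptions". The same treatment applies to both arms. Study design describes a "Phase III, multicenter, prospective, controlled, randomized superiority clinical trial". Sample size plans a two-sided test of proportions at α = 0.05 with 80% power for 0.60 (TEM) v 0.85 (CRT–TEM), and states that "53 patients per group are required to detect as significant a difference" and "Considering a 10% dropout rate, the total sample size will be 106 patients". Statistical analysis keeps all randomized patients in the principal analysis and announces pre-specified sensitivity analyses for missing primary endpoint data. The article gives no dropout rate by arm.

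**The concern.** Scoring missing as failure is conservative for a single-arm rate. In a comparison of two arms, the direction of the error depends on where the missing patients are. A patient who has had TME or a local recurrence is already a documented failure, so the rule changes the result only for patients who would otherwise count as preserved. The arm with more preserved rectums therefore has more to lose from the same proportion of missing patients.

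Two things are at stake. First, the power of the only confirmatory test: the sample size allows for dropout as though those patients left the denominator, while the analysis keeps them in as failures. Second, interpretation: the text tells the reader that any bias runs against the experimental arm, which need not be so.

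Deaths add to this. They open the same sentence as the rule, and a patient who has died has no documented 3-year status. The article does not say whether a death with the rectum in situ is a failure.

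**Working it through.** **Inputs from the article.** True rates 0.60 and 0.85, two-sided α = 0.05, 53 per arm, 10% dropout (Sample size); all randomized patients analysed (Statistical analysis); 5-year overall survival of 74% and 82% in two T1 local-excision series, and 82.7% and 85.2% in the arms of the group's earlier randomized trial (Introduction).

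**Assumptions.** Loss is independent of outcome, with share m in an arm; arm-specific values of m are illustrative. No interim adjustment of alpha is included.

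**The plan's own figure.** The arcsine formula has effect size h = 2·arcsin√0.85 − 2·arcsin√0.60 = 0.574, so n = 2(1.960 + 0.842)²/0.574² = 47.6 per arm. Dividing by 0.90 gives 52.9, so 53 per arm and 106 in total. The stated size therefore reproduces if 53 already contains the dropout allowance.

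**Model for the rule.** Observed preservation rate = true rate × (1 − m). Power and error are obtained by exact enumeration of two binomials with 53 per arm, using the Pearson test.

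**True effect, equal loss in both arms.**

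| Loss per arm | Observed rates | Difference | Power |
|---|---|---|---|
| 0% | 0.600 v 0.850 | 25.0 points | 84.5% |
| 5% | 0.570 v 0.8075 | 23.75 points | 77.1% |
| 10% | 0.540 v 0.765 | 22.5 points | 70.0% |

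At 10% loss, CRT–TEM gives up 0.85 × 0.10 = 8.5 points and TEM 0.60 × 0.10 = 6.0 points. The allowance was built for a different case: 53 × 0.90 ≈ 48 evaluable patients per arm at undiluted rates, where the normal approximation gives 79.3% power.

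**No true effect: chance of a significant result favouring CRT–TEM.**

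| Loss TEM v CRT–TEM | True rate 0.60 in both | True rate 0.85 in both |
|---|---|---|
| 0% v 0% | 2.6% | 2.4% |
| 10% v 10% | 2.3% | 2.6% |
| 10% v 5% | 4.7% | 7.8% |
| 10% v 0% | 8.9% | 19.8% |
| 5% v 15% | 0.4% | 0.1% |

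**Deaths counted as failures.** With constant hazard and equal mortality in both arms, 3-year survival = (5-year survival)^(3/5). No other loss is added.

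| 5-year OS | 3-year OS | Observed rates | Power |
|---|---|---|---|
| 74% | 83.5% | 0.501 v 0.710 | 60.8% |
| 82% | 88.8% | 0.533 v 0.755 | 68.3% |
| 82.7% | 89.2% | 0.535 v 0.758 | 68.9% |
| 85.2% | 90.8% | 0.545 v 0.772 | 71.1% |

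The lowest survival comes from the group's own T1 cohort, where "Five-year rectal cancer–specific and overall survival rates were 95% and 74%, respectively". The gap between the two rates suggests that most of those deaths were not from rectal cancer.

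**The case against.** A good part of the opposing case stands.

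- With equal loss there is no excess of false benefits, and at the planning rates the rule leans against CRT–TEM, which is roughly what the label claims. The observed difference is 0.25 − 0.85·m(CRT–TEM) + 0.60·m(TEM). It is inflated only when TEM loss exceeds 0.85/0.60 ≈ 1.42 times CRT–TEM loss. With 12% in TEM v 10% in CRT–TEM it still shrinks, to 0.25 − 0.085 + 0.072 = 0.237.
- A reader might infer that the rule can create a false CRT–TEM benefit as easily as it can hide a true one. The documents do not support that. A false benefit needs materially more loss in TEM, and nothing in the article gives a reason to expect it.
- Sensitivity analyses are announced in two places. Their detail may sit in an analysis plan that is not shown, so its absence from the article is no fault.
- The 61% power figure rests on the least favourable survival series; the others give 68–71%.
- Missing = failure is transparent and keeps every randomized patient. A competing-risk cumulative incidence would change what is estimated, because death with the rectum in situ would stop being a failure. It also fits poorly with permanent stoma, which is defined as a status at 3 years.

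These points do not rescue the rule as written. Sensitivity analyses leave the primary test unchanged, and the loss of power arises with equal loss at the plan's own dropout figure.

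**Conclusion.** The concern holds in a limited form. The conservative label is not guaranteed. The firmest consequence is dilution: at 10% loss in each arm, power is 70.0% against the stated 80%, because the dropout allowance does not offset losses that are scored as failures. This assumes that loss is independent of outcome and equal between arms.

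A raised false-positive risk for CRT–TEM (4.7–7.8% at 10% v 5%; 8.9–19.8% at 10% v 0%, against about 2.5%) is conditional on excess loss in TEM. It is a possibility that the label conceals, not a prediction. The upper ends also require a true rate of 0.85 in both arms, above the 0.60 planned for TEM.

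If deaths are covered by the rule, as the text suggests without saying so, power is about 61–71% under constant hazard and equal mortality.

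**What to change.** In the primary endpoint section:

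1. Remove the adverb that calls the rule conservative.
2. State separately how a death with the rectum in situ and a loss to follow-up are counted.
3. For losses, keep the 3-year difference in proportions, but make multiple imputation by arm from the last documented 4-monthly visit the primary handling. Keep missing = failure as a sensitivity analysis.
4. Add the analysis that is conservative for superiority: undocumented CRT–TEM counted as failure, undocumented TEM as preserved.
5. Report missing status by arm and reason.
6. If missing = failure stays primary, restate power in the sample size section as about 70% at 10% loss.

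The cost is protocol and analysis-plan wording; the 4-monthly visits are already scheduled. The small downside is that imputation assumes loss is uninformative given the last visit, which the retained sensitivity analyses probe. A competing-risk cumulative incidence is an option, not a requirement.

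### Persistent local tumour without TME counts as rectal preservation while local recurrence without TME counts as failure, with no rule separating them; the sample size also uses a different definition of the endpoint

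*Protocol article*

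**What the plan says.** All references are to the protocol article.

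- **Primary variable (endpoint), core definition.** "Rectal preservation failure is defined as any completion TME due to protocol discontinuation criteria (e.g., adverse pathology or inadequate response"). A second limb covers surgery after relapse, namely "any salvage TME performed for local recurrence during follow-up". A later sentence extends failure to TME for any reason and to a permanent stoma at 3 years.
- **Same section, recurrence.** "Local recurrence will be considered a rectal preservation failure irrespective of the subsequent management strategy (including cases treated without TME").
- **Same section, unknown status.** Patients whose status at 3 years is not documented count as failures in the primary analysis.
- **Same section, last sentence.** "Patients who do not undergo TME for any reason but have persistent/uncontrolled primary disease will be counted as rectal preservation (rectum in situ"). It then treats these same patients as local failures and as DFS events.
- **Secondary variables, oncologic follow-up.** Local recurrence means adenocarcinoma on biopsy of the scar or excision bed, or pelvic nodes positive on puncture, assessed at 3 years. No tumour-free interval is required.
- **Sample size.** The endpoint is "rectal preservation, defined as the absence of the need for completion TME due to discontinuation criteria or local recurrence and rescue to TME". The supporting inputs are rates of pathology: sm3 in 35–40% and adverse factors in 5–10%. The assumed preservation rates are 0.60 (TEM) and 0.85 (CRT–TEM).

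**The concern.** There are two separate problems.

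**Local disease without TME.** Viable tumour in a rectum that has not been removed is a failure if called recurrent and a success if called persistent. The definition of recurrence does not separate the two. CRT cannot in practice be concealed from the treating team, so whoever applies the label is likely to know the arm. The ordering is also odd: a patient with documented uncontrolled tumour scores better than one whose status is unknown.

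**Need versus performance.** The sample size section counts a patient who needs completion TME as a failure. The endpoint section counts completion TME only when it takes place. A patient with an sm3 specimen who has no TME and stays disease-free is a failure under the first and preserved under the second.

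At stake is whether two analysts following the text would reach the same primary result, and whether 0.60 and 0.85 describe the endpoint that will be analysed.

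**Working it through.** **Step 1: set the rules side by side.** Every patient below has had no TME and has no permanent stoma.

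| Patient at 3 years | Endpoint section | Sample size section |
|---|---|---|
| Local recurrence | Failure | Not explicit (recurrence is coupled with rescue to TME) |
| Persistent/uncontrolled primary disease | Preserved, but local failure and DFS event | Failure if a completion criterion was met |
| Completion criterion met, disease-free | Preserved | Failure |
| Status unknown | Failure | Not addressed |

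**Step 2: test the overlap.** Take a patient whose excision margin is below 1 mm, who has no completion TME, and whose scar biopsy at the first 4-monthly visit shows adenocarcinoma. The biopsy meets the definition of local recurrence, so the patient is a failure. The patient also has primary disease that was never cleared and no TME, so the last sentence of the endpoint section makes the patient preserved. The article gives neither rule precedence.

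**Step 3: reproduce the stated sample size.** Inputs from the sample size section: p₁ = 0.60, p₂ = 0.85, two-sided α = 0.05, power 80%, 10% dropout.

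- Unpooled formula: n = (1.96 + 0.8416)² × (0.60×0.40 + 0.85×0.15) / 0.25² = 7.849 × 0.3675 / 0.0625 = 46.2, so 47 per arm. With dropout, 47/0.9 = 52.2, so 53.
- The pooled formula gives 49, and 49/0.9 = 54.4, so 55.

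The stated 53 per arm (106 in total) therefore reproduces if 53 already includes dropout.

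Power at n per arm, with p̄ the mean of the two rates and Δ their difference:

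Power = Φ{[Δ√n − 1.96√(2p̄(1−p̄))] / √(p₁(1−p₁) + p₂(1−p₂))}

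For n = 53: (0.25×7.280 − 1.96×0.6315)/0.6062 = 0.961, so power is 83.2%.

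**Step 4: illustrate the need-versus-performed gap.** Assume that 0.60 and 0.85 are need-based rates. Let r be the share of need-based failures with no TME who are scored as preserved. The documents give no value for r. The rate analysed becomes p + r(1 − p).

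| r, both arms | Rates (TEM vs CRT–TEM) | Difference | Power at 53 per arm |
|---|---|---|---|
| 0% | 0.600 vs 0.850 | 0.250 | 83.2% |
| 5% | 0.620 vs 0.8575 | 0.2375 | 80.4% |
| 10% | 0.640 vs 0.865 | 0.225 | 77.3% |
| 20% | 0.680 vs 0.880 | 0.200 | 70.6% |

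If only one arm is affected, the direction depends on which:

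- **CRT–TEM only.** r = 10% gives 0.60 vs 0.865 (power 88.0%) and r = 20% gives 0.60 vs 0.88 (91.9%). The gain is an artefact of scoring.
- **TEM only.** r = 20% gives 0.68 vs 0.85 and power of 54.2%, but only if local recurrences are rescored too, which the endpoint section forbids. Suppose 5 to 15 of the 40 percentage points of TEM failure are local recurrences (an assumption). Then 20% of the remaining 35 to 25 points moves, giving 0.67 to 0.65 vs 0.85 and power of about 58% to 67%.

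None of these figures sizes the persistent-disease rule. The documents give nothing from which to size it.

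**The case against.** **The two local-disease categories are named separately.** The article gives each its own rule, and it records persistent disease as a local failure and DFS event. This may be a deliberate choice to measure rectum in situ. With scar biopsies every 4 months, most persistent tumour would be proven by biopsy and so meet the recurrence definition. The remaining group is mainly patients with no excision or with known residual tumour. This stands as a limit on how many patients are affected. It does not remove the conflict, because the last sentence of the endpoint section still calls these patients preserved and no precedence is given.

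**The sample size wording may be only a recap.** The protocol expects an indicated completion TME to be carried out within 4–6 weeks, so need and performance part only when that step is not followed. This is fair, and it means the size of the gap depends on non-adherence that the documents do not quantify. But pathology that triggers an indication is the main stated input to the assumed rates, so the gap concerns a main component of the endpoint.

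**Stronger readings to avoid.**

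- A reader might infer that the trial is powered for the wrong endpoint, with true power near 54%. The documents do not support this. No refusal rate is given, 54% requires rescoring recurrences that always count as failures, and 5% in both arms still leaves 80.4%. It is also an assumption that 0.60 and 0.85 are purely need-based: sm3 plus adverse factors could reach 50% if they did not overlap, before upstaging or recurrence.
- A reader might infer that every unperformed indication must become a failure. That is a debatable redefinition. It would fail patients with an intact, disease-free rectum, and it would add a trigger (week-9 MRI restaging) that exists only in the CRT–TEM arm.

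**Conclusion.** The point holds as a conflict of definitions, not of arithmetic: the sample size reproduces. The scoring of local disease without TME should be settled before outcome data are seen, including at the interim analysis, because the present text allows opposite primary outcomes for one patient. The mismatch between need and performance is real and calls for alignment, but the documents do not dictate which definition to keep.

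The number of patients affected, and their split between arms, cannot be determined from the documents. Under the assumption that 0.60 and 0.85 are need-based, power at 53 per arm runs from about 80% to 71% for an assumed 5% to 20% rescored in both arms, against 83% for the planned rates. Non-performance confined to one arm could shift the result in either direction. These figures are illustrations, not estimates.

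**What to change.** 1. Replace the last sentence of the primary endpoint section. In the primary analysis, persistent or uncontrolled local disease at or before 3 years, with or without TME, is a rectal preservation failure. Whether disease is called recurrent or persistent then no longer affects the score.
2. Report rectum in situ / no TME performed as a secondary endpoint, so that the information in the present rule is kept.
3. State one definition of completion-TME failure, either indicated or carried out, in both the endpoint and sample size sections. Use the other as a sensitivity analysis, and base 0.60 and 0.85 on the one chosen.

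These changes concern outcome scoring only and leave patient management as it is. Items 1 and 2 use data already collected; their cost is a slightly lower stated preservation rate. Item 3 needs a decision by the sponsor and a check of the two assumed rates, and N changes only if those rates do.

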#### Secondary variables

CRT-related adverse events will be prospectively recorded and graded according to CTCAE v5.0 [47]. Acute toxicity will be collected from CRT initiation through 30 days after TEM, and late toxicity will be collected thereafter during follow-up up to 3 years.

*Quality-of-life outcomes* will be assessed using the EORTC QLQ-C30, EORTC QLQ-CR29, Wexner, and LARS questionnaires before surgery and at 12 months. Clinical response to CRT will be evaluated using the predefined multimodal clinical assessment.

*Demographic variables:* age, sex, and recruiting hospital.

*Preoperative or pre-neoadjuvant phase:* Baseline tumor characteristics will include tumor size (measured by colonoscopy, endorectal ultrasound [ER], and pelvic MRI; maximum diameter in mm), distance from the anal verge, tumor location (anterior, posterior, right or left lateral), percentage of rectal circumference involved, ER and MRI staging, presence of distant metastases (thoracoabdominal CT), preoperative tumor markers (CEA and CA 19–9), and histological grade on biopsy. After completion of neoadjuvant chemoradiotherapy and prior to local excision, clinical response will be assessed using a multimodal approach integrating digital rectal examination, endoscopy, and pelvic MRI, and will be categorized as complete, near-complete, or incomplete clinical response, according to predefined criteria.

*Surgical variables*: the technique employed, operative time, estimated blood loss, intraoperative complications, conversion to abdominal surgery, en bloc resection, and closure of the defect.

*Pathological variables*: tumor size, differentiation grade, response grade to CRT, pT stage, venous, lymphatic, or perineural invasion, tumor budding, local excision specimen margins (minimum lateral and deep distances, in mm), presence of muscularis propria, residual healthy submucosa/submucosal invasion, and sm classification according to Taulí-pT1.

*Postoperative morbidity:* will be classified according to the Clavien–Dindo system and also expressed using the Comprehensive Complication Index (CCI). The primary analysis will be performed at 30 days, and complications will be recorded up to 60 days to capture clinically relevant late events. Length of hospital stay, readmissions, and mortality will also be documented. Postoperative morbidity will be captured not only after local excision but also after any completion or salvage TME, using the same definitions and time windows (30 and 60 days).

*Oncologic follow-up:* LR (defined as adenocarcinoma in the biopsy of the scar or excision bed, or positive pelvic lymph nodes on puncture, assessed at 3 years), DS, OS, DFS and rectal cancer–specific survival.

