### Secondary objectives

To assess the tolerance and adverse effects (acute and chronic) of preoperative chemoradiotherapy (CRT) in the CRT–TEM group (patient safety). To analyze postoperative morbidity and mortality in both groups (surgical outcomes). To evaluate clinical and pathological responses to CRT. To assess quality of life at 1 year after surgery in both groups. To compare long-term oncologic outcomes between groups (at 3 years): LR, DR, DFS, OS and rectal cancer–specific survival at 3 years.

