### Chemoradiotherapy-TEM group (CRT-TEM)

#### Neoadjuvant treatment: preoperative CRT (long-course regimen)

Neoadjuvant chemotherapy will be administered concomitantly with radiotherapy and will consist of oral capecitabine 825 mg/m^2^ every 12 h on radiotherapy days.

Long-course radiotherapy will be administered using one of the following techniques, depending on institutional availability, with preference for the first:Volumetric modulated arc therapy (VMAT). Two treatment fields will be defined. Primary (standard) field includes the tumor, the mesorectum, and the regional pelvic lymph nodes, delivering a total dose of 45 Gy in 25 fractions (1.80 Gy/fraction). For the elective pelvic CTV, the cranial border will be set at the S2–S3 junction to minimize toxicity in this cT1N0M0 population. Cranial extension up to the sacral promontory/common iliac bifurcation may be considered only when clinically indicated (e.g., higher tumor location or suspicious nodal disease). Boost field: includes the tumor area and any pathological adjacent lymph nodes, delivering a total dose of 50 Gy in 25 fractions (2.00 Gy/fraction). An integrated boost technique, inherent to VMAT, will be used [38].Conventional three-dimensional planning (3D-CRT). The same target volumes as in (1) will be treated but using a sequential boost: 45 Gy in 25 fractions to the primary field, followed by 5.40 Gy in 3 fractions to the boost field. This schedule results in 28 treatment sessions, with the same fractionation (1.80 Gy/fraction) [39, 40].

At week 9 after completion of CRT, clinical response will be assessed by pelvic MRI, endoscopic and digital rectal exam [41]. CRT-related adverse events will be prospectively recorded and graded according to CTCAE v5.0. Acute toxicity will be collected from CRT initiation through 30 days after TEM, and late toxicity will be collected thereafter during follow-up up to 3 years.

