### TEM group (TEM)

Patients assigned to the TEM group will undergo transanal endoscopic microsurgery, following the same local excision procedure described above.

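### CTCAE-graded acute and late toxicity is collected only as CRT-related events, so this part of safety cannot be compared with TEM alone, although the design states a comparative safety evaluation

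*Protocol article*

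**What the plan says.** The Protocol article, Study design, describes a phase III trial "evaluating the efficacy and safety of preoperative CRT followed by LE (CRT-TEM group) versus LE alone (TEM group"). Read plainly, that is a comparison of safety between the arms.

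Secondary objectives splits safety in two. The item labelled patient safety is confined to one arm: "To assess the tolerance and adverse effects (acute and chronic) of preoperative chemoradiotherapy (CRT) in the CRT–TEM group (patient safety"). The next item covers both: "To analyze postoperative morbidity and mortality in both groups (surgical outcomes").

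The toxicity rule appears twice in almost the same words, once under the CRT–TEM arm's neoadjuvant treatment and once under Secondary variables: "CRT-related adverse events will be prospectively recorded and graded according to CTCAE v5.0". Its time windows are: "Acute toxicity will be collected from CRT initiation through 30 days after TEM, and late toxicity will be collected thereafter during follow-up", to 3 years. The TEM group section describes only the operation: "Patients assigned to the TEM group will undergo transanal endoscopic microsurgery, following the same local excision procedure described above".

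The Discussion names acute and late pelvic toxicity as the trade-off of giving CRT in cT1N0M0 disease. It says the long-term implications will be monitored by recording acute and chronic CRT-related events.

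**The concern.** The main argument against CRT in this population is the toxicity it may add to an operation that is already standard. To estimate that addition, the same events must be counted in both arms, on the same scale and over the same period. Here the graded count exists only where CRT was given, and only for events judged to be caused by it.

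Two problems follow. Rectal bleeding, urinary symptoms or bowel events also occur after excision alone, and that background rate is not measured on the CTCAE scale. In addition, the acute window in CRT–TEM runs through the operation and 30 days beyond it, so an event in that period has to be assigned to CRT or to surgery by someone who knows the patient was irradiated, with no control rate against which to check the judgement.

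If rectal preservation improves, the readers who must weigh it against late pelvic toxicity would have a one-arm, attributed count for that part of the cost.

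**Working it through.** The plan gives no figure on this point, so the check sets the sections side by side and then measures the windows.

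**Harm data by arm, as stated**

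| Measure | Period | CRT–TEM | TEM | Section |
|---|---|---|---|---|
| CTCAE v5.0, acute, CRT-related | CRT start to 30 days after TEM | yes | no counterpart | Neoadjuvant treatment; Secondary variables |
| CTCAE v5.0, late, CRT-related | thereafter to 3 years | yes | no counterpart | same |
| Clavien–Dindo and Comprehensive Complication Index | 30 and 60 days after excision and after any completion or salvage TME | yes | yes | Secondary variables |
| EORTC QLQ-C30 and CR29, LARS, Wexner | baseline and 12 months | yes | yes | Study procedures; Follow-up |
| Mortality, overall survival | postoperative; 3 years | yes | yes | Secondary objectives; Secondary variables |

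The first two rows are one-armed by construction: a TEM patient has no CRT start and cannot have a CRT-related event.

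**Length of the windows**

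Inputs: 25 or 28 fractions and excision at week 10 (CRT–TEM arm sections); 30 days after TEM (toxicity rule); 60 days (postoperative morbidity). Assumptions: five fractions per week, and week 10 taken as 70 days.

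- CRT duration: 25/5 = 5.0 weeks = 35 days; 28/5 = 5.6 weeks, about 39 days.
- CRT start to excision: 35 + 70 = 105 days; 39 + 70 = 109 days. Postoperative morbidity scoring starts at surgery and so does not cover this period.
- Acute window: 105 + 30 = 135 days; 109 + 30 = 139 days.
- TEM arm after excision, no further operation: 3 × 365 = 1,095 days; 1,095 − 60 = 1,035; 1,035/1,095 = 0.945, about 95% of follow-up days without a stated graded clinical event record.

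The last figure describes time without Clavien–Dindo or CTCAE grading. It is not the share of safety information that is missing, because the 12-month questionnaires fall inside that period.

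**The end of the acute window**

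Criteria for exiting the study protocol sends patients restaged at week 9 as ≥ cT2 and/or cN1 to TME. They have no TEM, so the point 30 days after TEM does not exist for them, and neither the end of the acute window nor the start of the late one is defined.

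**What a two-arm comparison could show**

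With 53 patients per arm and, as an assumption, the same event rate p in each, the half-width of the 95% confidence interval for a difference is 1.96 × √(2p(1 − p)/53):

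- p = 0.05: 0.083
- p = 0.10: 0.114
- p = 0.20: 0.152

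The comparison would be an estimate with a wide interval, suited to reporting by arm and not to a powered test.

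**The case against.** A reader might infer that the trial cannot compare safety at all, and that a benefit would be reported with no randomised estimate of its cost. The document does not support that. Surgical morbidity is scored in both arms, including after completion or salvage TME, so the harm avoided by fewer TMEs is partly captured. The Discussion names urgency, frequency, incontinence and LARS as possible harms of CRT and assigns them to the questionnaires, which both arms complete at baseline and 12 months. The Hypothesis section limits its own no-harm statement to postoperative morbidity and quality of life, and both are measured in both arms.

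A reader might also infer that later events in TEM patients will go entirely unrecorded. That goes too far. Study monitoring mentions pharmacovigilance, and the full protocol of a regulator-authorised medicines trial may contain general adverse-event reporting that an article leaves out.

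These points narrow the concern but do not remove it. Postoperative scoring starts at surgery and stops at 60 days. The questionnaires give one time point after treatment, do not grade clinical events such as bleeding, and are silent on months 12 to 36. The pharmacovigilance remark gives no arm, grading or window. The restriction to CRT-related events is not an article's silence: it is stated in the objectives, twice in the methods, and again in the Discussion.

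The undefined acute window is the lesser matter. Collection continues to 3 years in any case, so the acute or late label is unclear but no loss of data is stated.

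**Conclusion.** The point holds in limited form. Graded non-surgical acute toxicity, and graded late pelvic events from day 60 to 3 years, have no stated parallel record in the TEM arm, and in CRT–TEM they depend on attribution by people who know the treatment. This does not match the comparative safety aim in Study design. The arms can still be compared on postoperative morbidity, 12-month function and quality of life, and mortality and survival.

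The gap covers about 95% of follow-up days after excision for a TEM patient with no further operation, plus the roughly 105 to 109 days from CRT start to excision in the other arm. These lengths assume five fractions per week and surgery on day 70. Nothing here affects the primary endpoint or its sample size. The change should be made, but the trial does not fail without it. Confidence is moderate, because the full protocol is not shown and might already record events in both arms.

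**What to change.** In the neoadjuvant treatment section and in Secondary variables, replace the CRT-related restriction with one rule for both arms. Record and grade by CTCAE v5.0 the same list of clinically ascertained pelvic, bowel, urinary, sexual and wound events, regardless of judged cause, from randomisation to 3 years. Use the 4-monthly visits already in Follow-up. Report the events by arm with confidence intervals, and keep attribution to CRT as a descriptive field.

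Leave laboratory toxicity as monitoring in the CRT arm. The only follow-up blood tests listed are CEA and CA 19–9, so a haematological comparison would need new tests.

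Define the acute window by time from randomisation, or by the first operation of any kind. Either gives it an end for patients who go to TME without TEM. Time from randomisation also gives both arms a window of equal length.

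If this is not done, narrow the safety wording in Study design to the outcomes measured in both arms.

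The cost is a wording change, added eCRF fields and data entry for TEM patients, with no new visits, procedures or patients. One weakness remains: early events in TEM patients would be observed less closely than events during CRT attendance, and the report should say so.
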